## Abstract

**Background:**

First-year university students are at an increased risk for developing mental health issues and a poor nutritional status. Self-care plays an essential role in optimizing mental health and can prevent or manage stress, anxiety, and depression. Web-based self-monitoring of diet and physical activity can lead to similar or improved health outcomes compared with conventional methods. Such tools are also popular among university students.

**Objective:**

The primary aim of this 12-week randomized controlled trial is to assess the impact of a web-based wellness platform on perceived stress among first-year university students. The secondary aim is to assess the effects of the platform on diet quality. The exploratory objectives are to explore the effects of the platform on body composition, health-related quality of life, mindfulness, mental well-being, and physical activity.

**Methods:**

A total of 97 first-year undergraduate students were randomized to either the intervention (n=48) or control (n=49) group. The intervention consisted of access to a web-based platform called My Viva Plan (MVP), which aims to support healthy living by focusing on the topics of mindfulness, nutrition, and physical activity. The platform is fully automated and guided by the principles of cognitive behavioral theory. Participants in the intervention group were instructed to use the MVP as frequently as possible over 12 weeks. The control group did not receive access to MVP. Perceived stress was assessed using the Stress Indicators Questionnaire at baseline, week 6, and week 12. Three-day food records were used to analyze the dietary intake at baseline and week 12. Health-related quality of life, mindfulness, mental well-being, and physical activity questionnaires were completed at baseline, week 6, and week 12. Body composition was assessed at baseline and week 12. Study assessments were completed in person at baseline and week 12 and electronically at week 6.

**Results:**

Study recruitment started in August 2018, with batch enrollment for students registered in the fall (September 2018 to December 2018) and winter (January 2019 to April 2019) academic terms at the University of Alberta, Edmonton, Alberta.

**Conclusions:**

This study is the first to explore the impact of a web-based platform designed to promote health and wellness on perceived stress and diet quality among first-year university students.

**Trial Registration:**

ClinicalTrials.gov NCT03579264; https://clinicaltrials.gov/ct2/show/NCT03579264.

**International Registered Report Identifier (IRRID):**

DERR1-10.2196/24534

## Introduction

### Background

University students are at risk of developing mental [1] and physical [2-4] health problems. The number of students reporting symptoms of anxiety [5], depression [5], and suicidal thoughts [1,6] continues to rise, and this is a greater concern among first-year undergraduate students [7]. During this important yet vulnerable period of their lives, students not only transition from adolescence to adulthood but also start to face challenging situations and the new responsibilities of career development and a self-sufficient life [8]. This specific period and situation is related to neurobiological, behavioral, and environmental changes that impose significant psychological stress [9,10] and an increase in the risk of psychiatric disorders [11].

In addition to mental health, during the first year of a university program, students’ dietary habits and physical activity are also negatively impacted [2,3,12,13]. Students increase their consumption of unhealthy, energy-dense foods and reduce their intake of healthy, nutrient-dense foods in their first year of university, resulting in an overall decrease in diet quality [13]. These changes may result in unfavorable alterations of their nutritional status, such as an increase in body weight and fat mass [3,13,14]. In a meta-analysis of 5549 university students, the mean weight change during the first year was 1.36 kg (95% CI 1.15-1.57 kg) [15]. Hoffman et al [3] observed an increase of 0.7% of fat mass among first-year university students, which further illustrates the physical changes that are observed in this population.

Increased psychological stress and poor nutritional status can hinder students’ quality of life [16], hinder academic performance [17], and increase morbidity [18] and mortality [19]. Apart from the direct impact on students, mental health problems in the general population and workforce impose a significant financial burden on the health care system [20,21]. Universities may be the last setting in which mental health programs can be promoted to a large portion of young adults before they enter the diversified workforce [22]. Therefore, the development of programs focused on the mental and physical health status of university students is of special interest.

University students rely heavily on technology to perform tasks of daily living, and health care is no exception [23]. The use of electronic tools to monitor health status is increasing in the general population. Of the expected 80-100 billion smart devices in the world by 2020, approximately 26 billion will be used to monitor aspects of personal health and well-being [23]. Therefore, individualized technological tools encompassing aspects of practicality, availability, cost, and time efficiency are promising health promotion approaches for this generation (ie, generation Z).

Research has shown that electronic monitoring of diet or diet and physical activity can lead to similar or better health outcomes compared with conventional methods such as paper-based food records and weight loss resulting from counseling with practitioners [24-27]. Although digital health apps for nutrition, physical activity, and mental health are extremely popular among young adults [28], many of these tools have not been designed by health care professionals [29,30] and lack a sound evidence base [31]. Moreover, previous research has shown that poor integration between nutrition and physical activity apps or trackers is a concern among users [32].

Considering the limitations of many available eHealth tools, My Viva Plan (MVP; Multimedia Appendix 1) [33] addresses some common shortfalls as it was developed by a registered dietitian ([name], Revive Wellness Inc) in collaboration with other health care professionals (registered psychologists, certified personal trainers, and kinesiologists). It focuses on multiple pillars of health: mindfulness, nutrition, and physical activity. MVP is a publicly accessible web-based program available via paid subscription. The platform can be used as a stand-alone intervention or in combination with coaching from professionals. MVP has 3 variations of the platform to target different populations: 1 variation targeted at the general population and 2 variations targeted at students attending local postsecondary institutions. The variation used and described in this study is the variation that is targeted at students attending the University of Alberta (Edmonton, Alberta).

### Objectives and Hypothesis

The main objective of this 12-week randomized controlled trial is to assess the impact of MVP on perceived stress among first-year university students. The secondary objective is to assess the impact on diet quality, and exploratory objectives will assess the impact on body composition, health-related quality of life, mindfulness, mental well-being, and physical activity. It was hypothesized that using an integrated web-based wellness platform that encompasses the 3 pillars of preventative self-care (mindfulness, nutrition, and physical activity) would help guide health behavior, resulting in improved perceived stress and diet quality in first-year university students.

## Methods

### Study Design and Ethical Considerations

This 2-armed, parallel, randomized controlled trial was conducted at the Human Nutrition Research Unit (HNRU), University of Alberta, and used an embedded mixed methods design [34,35]. The research protocol is approved by the University of Alberta Ethics Board (Pro00079680) and complies with the standards set out in the Canadian Tri-Council Policy statement on the use of human participants in research. Before the commencement of the study, all participants were informed in person of the procedures and potential risks involved in the investigation and were asked to provide written informed consent. All participants, regardless of group assignment, received CAD $50 (US $39) cash and one year of free membership to MVP after completing all study assessments.

### Research Participants

First-year undergraduate students at the University of Alberta were recruited using a variety of techniques (in-class invitations, in person through flyers distributed at special events and locations, email, social media, and advertisements placed on notice boards on campus) during the fall (September 2018 to December 2018) and winter (January 2019 to April 2019) terms. Various campus faculties were targeted for recruitment to ensure a diverse sample. Eligible participants were males and females aged 17-30 years who were able to complete all study assessments in their first year of undergraduate studies. Reasons for exclusion included any self-reported eating disorder; self-reported untreated depression, anxiety, or mood disorder; pregnancy or lactation; not having a device to access the internet (ie, computer, smartphone, tablet); not able to communicate in English; or having an electronic implantable device (because of body composition assessment). Participants were assumed to have strong computer and internet literacy, given the typical age and education level of the study population; however, literacy levels of the participants were not assessed.

### Screening, Randomization, and Treatment Allocation

Potential participants contacted the research team and underwent prescreening using the same method in which they contacted the research team (ie, via email or over phone). The research team discussed the responsibilities of the participants (ie, time commitment of each study visit and a commitment of 12 weeks of participation) and addressed any questions before scheduling the baseline visit. The screening criteria were later confirmed and documented in person at the baseline visit. A member of the research team reviewed the study consent form in detail with each participant during their baseline visit, and participants received a copy of their signed study consent form for their records. All eligible and consenting participants were randomly assigned by block randomization to the intervention (platform use) or control (no intervention) group in a 1:1 allocation ratio. Blocks were stratified by sex to balance sex distribution and block sizes randomly alternated between blocks of 2 and 4 to minimize the risk of predictable group allocation [36].

The allocation sequence was generated by an independent biostatistician and uploaded onto Research Electronic Data Capture (REDCap) [37,38], where it was concealed from the study team. The study team enrolled and assigned the participants to the groups using REDCap. The participants and researchers were not blinded to the group assignment because of the nature of the study. The staff needed to know the participants’ group assignment to provide access to the platform, monitor use, and schedule interviews.

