### Statistical Analysis and Power and Sample Size Rationale

#### Statistical Analysis

Our analysis of the primary outcome will be based on an intention-to-treat analysis using inverse probability weighting. Our analysis of the secondary and exploratory outcomes will be based on per-protocol and intention-to-treat analyses using inverse probability weighting. The effects of intervention over time will also be investigated using a generalized estimating equation. SPSS 25 (IBM Corporation) statistical software will be used for the data analysis. Characteristic variables will be compared between the 2 treatment groups and between those that did and did not complete the study. Differential variables will be used as covariates in the statistical analyses. *P*<.05 will be considered statistically significant.

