## Results

Study recruitment began in August 2018. Batch recruitment was used for enrollment in the fall (September 2018 to December 2018) and winter (January 2019 to April 2019) terms, with 37 and 43 participants completing the study in the fall and winter terms, respectively. A total of 80 participants completed the 12-week trial (n=35 in the intervention group; n=45 in the control group; Figure 2).

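### Sex stratifies the randomisation but is not a prespecified covariate, and the plan's rule of adjusting for variables that differ will often leave it out

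*Protocol article*

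**What the plan says.** Under Screening, Randomization, and Treatment Allocation, sex is the only stratification factor: "Blocks were stratified by sex to balance sex distribution and block sizes randomly alternated between blocks of 2 and 4". Allocation is 1:1, and the abstract reports that 97 students "were randomized to either the intervention (n=48) or control (n=49) group".

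The Statistical Analysis section bases the primary analysis on intention to treat with inverse probability weighting. It names no covariate for the outcome model and no variable for the weight model. It does fix how covariates are chosen. First, "Characteristic variables will be compared between the 2 treatment groups and between those that did and did not complete the study". Then, "Differential variables will be used as covariates in the statistical analyses".

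Sex is among the demographic variables collected (Other Assessments), so the rule can consider it. Enrolment came in two batches, fall and winter, "with 37 and 43 participants completing the study in the fall and winter terms, respectively". Term is not a stratification factor and is not in the list of collected characteristics. By arm, the completers were "n=35 in the intervention group; n=45 in the control group".

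**The concern.** When randomisation is stratified, the treatment estimate varies less from trial to trial, because the stratifying factor cannot fall unevenly across the arms. The analysis shows this gain in its standard error only if the factor is in the model. Left out, the variance between strata goes into the error term, the standard error is too large and the test is conservative.

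The rule here works against the design. Its between-arm part looks for imbalance in the one variable that the design prevents from being imbalanced. The article commits to this rule, so the point is not about detail left to another document: an analysis plan that follows the article would inherit it. At stake are a little precision and power, and a primary model whose covariates depend on the data.

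**Working it through.** **No figure of the plan to reproduce.** The article gives no adjusted or unadjusted precision figure, no sex split and no sex effect. Those below are assumptions, shown as ranges.

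**Inputs from the article.** 97 randomised (48 and 49); blocks of 2 and 4 within sex; 80 completers (35 intervention, 45 control); significance at p<0.05.

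**1. Can the between-arm comparison select sex?** An unfinished block of 4 leaves a sex stratum out of balance by at most 2. I took every sex split with at least 10 students of each sex, every end-of-block imbalance from −2 to +2 that is compatible with arms of 48 and 49, and computed the uncorrected chi-square test.

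- Most extreme case: 10 of one sex split 6/4 and 87 of the other split 43/44. Chi-square = 0.401, p = 0.53.
- With at least 29 of each sex, the smallest attainable p is 0.71.

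In simulated trials under these blocks, sex was selected in 0%.

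**2. Can the completer comparison select sex?** Non-completers number 97 − 80 = 17 (17.5%): 48 − 35 = 13 in the intervention arm (27.1%) and 49 − 45 = 4 in the control arm (8.2%). Stratification does not constrain this comparison. Simulating 97 students at 17.5% overall dropout, with 50% or 70% women, sex was selected as follows.

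| True dropout difference between the sexes | Share of trials in which sex is selected |
|---|---|
| 0 points | about 5% |
| 10 points | 23% to 25% |
| 20 points | 65% to 76% |

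So sex can enter by this route, but dependably only if dropout differs strongly by sex.

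**3. What does omission cost?** Let π be the share of women and g the sex difference on the analysed outcome, in within-sex SDs. With sex balanced across arms:

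- standard error ratio = √(1 + π(1 − π)g²)
- true two-sided type I error = 2[1 − Φ(1.96 × ratio)]

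For π = 0.6:

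- g = 0.3: √(1 + 0.24 × 0.09) = √1.0216 = 1.011, type I error 4.8%
- g = 0.5: √(1 + 0.24 × 0.25) = √1.06 = 1.030, type I error 4.4%

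Over π from 0.5 to 0.7 the standard error excess is 0.9% to 3.1% and the type I error 4.3% to 4.8%.

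**4. Power** (normal approximation, Φ(d/SE − 1.96 × ratio), SE = √(1/n₁ + 1/n₂); the ratio is 1 when sex is adjusted for). The value 0.74 is the article's effect size; 0.50 is an assumed smaller effect.

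| Numbers analysed | Effect d | Adjusted | Unadjusted, g = 0.3 to 0.5 |
|---|---|---|---|
| 49 and 48 | 0.74 | 95.4% | 95.2% to 94.8% |
| 49 and 48 | 0.50 | 69.2% | 68.6% to 67.1% |
| 45 and 35 | 0.74 | 90.7% | 90.4% to 89.7% |
| 45 and 35 | 0.50 | 60.2% | 59.5% to 57.9% |

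The loss is about 0.2 to 2.3 points. It nears 6 points (60.2% to 54.3%) only with an assumed sex effect of 0.8 SD and d = 0.50. The rows for 45 and 35 also assume that sex stays balanced among completers, which the article does not show.

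**The case against.** The strongest reply is that the rule has two parts and that the second, between completers and non-completers, can bring sex in. That stands. A reader might infer from the between-arm argument that sex and term are shut out of the analysis; the article does not support this. It shows only that neither is prespecified. The weight-model variables are not given either, so nothing shows that sex is ignored there.

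Second, the primary outcome is the difference in change from baseline to week 12. A stable difference between the sexes in stress level cancels in a change score, and the loss is then near zero. This stands too: the 0.3 to 0.5 SD must be read as an effect on the analysed outcome.

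Third, a reader might extend the argument to academic term, since "Batch recruitment was used for enrollment in the fall (September 2018 to December 2018) and winter (January 2019 to April 2019) terms". Term was not stratified, so design and analysis do not conflict there; small sequential blocks merely tend to keep it near balance. Adding an assumed term effect of 0.5 SD to a sex effect of 0.4 SD would give 0.24 × 0.16 + 0.25 × 0.25 = 0.101, a standard error about 5% too large and a type I error of 4.0%. But 0.0625 of that 0.101 comes from the term effect, for which the article gives no figure.

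Fourth, a reader might infer confounding among completers. That would need dropout related to sex or term, and the plan answers it in part through the completer comparison, the weighting and its stated intention, under Limitations, to examine systematic differences. It also rests on imbalance among those analysed, the opposite of the premise behind the precision figures.

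What the reply does not remove is that inclusion of the stratification factor is left to one test that cannot realistically select it and another that rests on 17 dropouts.

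**Conclusion.** The point holds as a minor one, for sex. The stratification factor is not prespecified, and the rule for choosing covariates will often omit it. The size given in the brief rests on three assumptions: a sex effect of 0.3 to 0.5 SD on the analysed outcome, between 50% and 70% women, and balance of sex across the arms as analysed. If sex predicts stress level but not change, the loss is close to nil. The documents do not support a stronger conclusion, whether that sex cannot enter at all, that term shares the same defect, or that the treatment estimate is biased.

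**What to change.** In the Statistical Analysis section, state that sex is a fixed covariate in the primary, secondary and exploratory between-group models and in the model for the inverse probability weights, whether or not it differs between arms or between completers and non-completers. This replaces reliance on selection by observed difference. Academic term (fall or winter) may be named as an optional precision covariate; the Results section counts completers by term, so it is on record.

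The cost is a sentence of wording, fixed before the outcome data are analysed, and one degree of freedom, or two with term. No new data are needed. This is a free improvement.

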### Experimental Protocol

Participants allocated to the intervention group were instructed to use MVP as frequently as possible for the duration of the 12-week period. Participants allocated to the control group were asked to maintain their usual lifestyle throughout the study and did not receive access to MVP during the 12 weeks of study participation. In-person study visits occurred at baseline and week 12 at the HNRU (Figure 1), and the following assessments were collected: academic information, anthropometry, body composition, demographics (at baseline only), dietary intake, food security, health-related quality of life, mindfulness, mental well-being, perceived stress, and physical activity (Multimedia Appendix 2). At week 6, questionnaires were electronically administered (Figure 1) and collected via web-based surveys through REDCap [37,38] to assess food security, health-related quality of life, mindfulness, mental well-being, perceived stress, and physical activity (Multimedia Appendix 2). Participants assigned to the intervention group were asked to evaluate MVP by questionnaire at their week 12 visit and participate in a one-on-one semistructured interview to gather qualitative information on their experiences with and perceptions of MVP. Details of the qualitative analysis are published in a separate publication.

**Figure 1 figure1:**
[figure not shown]
Outline of the experimental protocol.

### Intervention

The principles of cognitive behavioral theory (CBT) [39], specifically the social cognitive theory of self-regulation [40], were used to guide the development of the MVP platform. The goal is to build resilience and self-efficacy through the development of strong self-care habits. The platform included features such as goal setting, diet plans, exercise tutorials, and self-monitoring of health behaviors (ie, stress levels). The variation of the platform used in our study was fully automated, with no human interaction. The University of Alberta logo is displayed on the log-in page of MVP and on any exercise video made in collaboration with the University of Alberta’s Campus and Community Recreation facilities; however, institutional logos were not present anywhere else within the platform.

All participants in the intervention group received free access to the same version of the MVP, and membership access was delivered by email within 5 days of completing baseline assessments. While using the platform, users were prompted to create a profile and fill in the basic medical history questions, including food allergies, medical conditions, and current medications. A video tutorial provided guidance on the platform and recommended that new users start with the mindfulness component. The tutorial explained that each component of the platform can be used independently or in combination and that users could set up a shortcut on their mobile device to directly access the MVP platform. No additional MVP training was provided by the researchers.

The 3 core components of MVP are described as follows:

My Mind encourages goal setting, daily reflections, and quarterly stress assessments. One of the first steps in setting up an MVP account is the goal-setting process. The platform allows users to set a maximum of 3 short-term and 3 long-term goals. Participants set their own goals, which could be modified at any time. The platform also advises users to keep their goals specific, measurable, achievable, realistic, and time-oriented. Examples of goals include “I will stretch every night before bed” (short term) and “I will train for a marathon this year” (long term). Daily reflections on stress levels, eating habits, physical activity, and steps taken toward achieving goals are encouraged. On the basis of the responses from the daily reflections, the user’s progress is viewable in a graphical format (such as a bar graph to indicate the level of stress on each day of the week and a checkmark on days of the week that steps were taken to achieve goals).My Nutrition contains meal plans, recipes, grocery shopping list, cooking demonstrations, Vivapedia (an encyclopedia on the nutritional benefits of numerous food items and nutrients), and a guide with suggested menu items from restaurants and fast-food chains in Edmonton and on the University of Alberta’s campus. Meal plans allow users to create their own plans for meals each day or to have a plan built for them. When a user builds their own meal plan, the number of suggested portions of protein, grains, fruits, vegetables, dairy, and fat are generated by the platform to fit the recommendations of the Eating Well with Canada’s Food Guide [41], and the user can choose foods from each food group, either from a drop-down list or by manually entering the food item, to reach these targets. Menu plans built by the platform for the user are based on the user’s preferences and meet the recommendations of the 2007 Eating Well with Canada’s Food Guide [41]. Platform-derived meal plans can be customized for allergies, intolerances, and other food preferences (ie, vegetarian, gluten-free, nut-free, dairy-free) and provide brief instructions on how to prepare each meal. A serving size guide is available within the platform and as a printable handout. The recommended proportion of foods from each food category is represented as a dinner plate model for users to refer.My Fitness provides a physical activity scheduler and video tutorials for workouts and yoga. The workout tutorials have accommodations for self-described fitness level, equipment availability, and desired duration, whereas the yoga tutorials incorporate guided meditations and can be adjusted by self-described fitness level and desired duration. Video workouts included resistance training, aerobic exercises, and stretching. In addition, users can log the duration and intensity of their workouts completed outside the platform.

To help foster learning in a wide range of individuals, the platform provides educational resources in multiple formats, including video content and printable handouts. MVP employs strategies commonly used in clinical practice, such as CBT, into daily reflections of health behaviors. Outside of the platform, coaching tips that provide messages of healthy living (ie, being present, seeking accountability, healthy snacking, keeping active) are emailed on a weekly basis and presented in the same sequence for all users. Users also receive student-specific messages in key times throughout the academic year (ie, managing the first week of a new academic term, preparing for midterm exams, preparing for final exams). The content of these email messages is not tailored based on the user’s activity within the platform.

